### Setting, participants and recruitment

Each centre will define where they will conduct the local single-group interventional study. This can be either in a dental school clinic, in a dental schools’ community/hospital/school children’s clinics, or if these are not available due to the pandemic, in researchers’ private practices. Invitations will be sent to these clinics and upon interest to participate, the centre coordinator will explain the study, its purposes and procedures. When and if the clinics’ authorities accept to take part, corresponding invitation and information about the study will be sent to the participants’ parents (and children), together with written consent forms (Additional file 2). Written assent forms will be included in countries where it is required and also depending on the age requirement (e.g. in Colombia for children over 6 years) (Additional file 3).

The inclusion criteria are children: (1) aged 3–5 and 6–8 years old; (2) generally healthy, and (3) have parental consent and children’s assent (if needed). The exclusion criteria include children who: (1) have major systemic diseases or major mental/physical disability; (2) their family have plans to move during the study timeline, and (3) wear orthodontic appliances. The strategies to reach the target sample size at enrolment, include the motivation of parents through the invitation, explaining the advantages of having their children receiving a caries patient-centred care and risk-based prevention, and that they will be receiving printed didactic aids to improve the child’s oral health behaviours. Children who attend a different dental practice for care during the study period will be excluded.

Written consent forms signed by parents/carers and written assent forms (when these applies) signed by children will be collected from children interested in participating before the dental examination and treatment take place and subjects will be coded to keep confidentiality.

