For 1D, remote combined with in-office assessment will be conducted with parents, including social/medical/behavioural risk factors (6 items); protective factors (3 items), and oral hygiene (3 items) and dietary (5 items) oral-health behaviours [3, 9, 10, 29, 31–34, 36]. Clinical risk factors (5 items) will be assessed in the dental clinic with the children, as 2D assessments. After assessing dental biofilm (Silness and Löe modified, [37]) , the other clinical assessments are conducted after toothbrushing, with the aid of a WHO probe and drying tooth surfaces and/or removing any dental biofilm only with cotton rolls/gauze (without using compressed air/water). Assessments at the tooth-surface level include: (1) caries lesions staging and activity assessment using the visual ICDAS-merged Epi criteria (Sound, Initial, Moderate microcavity/shadow, Extensive) active/inactive [35], and (2) presence and status of fillings (Optimal, Acceptable or Not acceptable) and sealants (Optimal or Not acceptable), modified from Cvar and Ryge [38], and at the tooth-level: (1) missing due to caries; (2) tooth close to exfoliation, and (3) dental sepsis as a clinical consequence of untreated caries, with the PuIpal Involvement-Roots-Sepsis Index (prs/PRS) modified from the PUFA Index [39] with/without toothache. Routine bite-wing radiographs are not included and only used in specific cases based on clinical need, not as part of the study protocol. For 3D, after synthesis of information from steps 1D and 2D the examiner conducts the personalised care plan, jointly with the child’s parent and the external DP. At the individual-level, a designed matrix based on CCI [9] weighs up the risk and protective factors against each other, classifying the patient’s caries risk into low or high, with a respective 9-month or 3-month risk recall interval. Another matrix, taking into account the COM-B behaviour model [29] weighs up the adequate vs. inadequate oral hygiene and dietary habits behaviours against each other, classifying the patient’s oral-health behaviour into adequate, inadequate or very inadequate. The individual-level risk management decisions will include homecare and clinical approaches/interventions, according to CCI and adapted for the pandemic (with non-AGP and including remote appointments when possible), including implementing a short behaviour-change tool. At the tooth-surface level, according to the synthesis of the clinical assessments defined in 2D, the type of care is defined per surface with non-AGP as: none, active monitoring (AM), non-operative care (NOC), tooth-preserving operative care (TPOC), and at the tooth-level as endodontics or extraction [9, 9].

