### Interventions

The interventions of this single-group study correspond to the 4D, as consequent individual- and tooth-level management approaches/interventions, to be implemented by the external DP, when possible with remote care and only with non-AGP. At the individual level (Fig. 1), homecare approaches include for all patients, instructions on twice-a-day toothbrushing with ≥ 1000 ppm F, and for high-risk patients, increasing the toothpaste’s fluoride concentration and providing general oral-health improvement information; clinical approaches/interventions include 5% NaF varnish at basic management, T1 and T2; if it applies, high-viscosity glass ionomer ART sealants in Occlusal surfaces (under non-AGP conditions), and motivational engagement of patients and parents through the study-specifically designed Short Behaviour Change Tool (SBCT) [29]. The implementation of the SBCT consists of discussing with the parent each behaviour previously assessed as inadequate (Fig. 3). First, setting a goal to be accomplished (e.g. “Do you think you could incorporate at any point during the child’s evening activities toothbrushing using fluoride toothpaste every night?”); then, planning together how best to achieve it and supporting it with a didactic aid (e.g. a tooth-brushing adhesive instructive diagram for the bathroom mirror), and plan for self-monitoring (e.g. calendar to mark the daily activity). Low-risk patients receive the didactic aids but no behaviour change is conducted.

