#### Secondary health outcomes

Proportion of subjects with avoidance of caries progression (ICDAS-merged Epi severity and/or activity).Proportion of subjects with avoidance of caries risk level increase/no control, and avoidance of extraction, pain, failure of the filling/sealant.Proportion of parents and dentists with high dental care process acceptability (measured with TEI).Proportion of children improving oral-health related behaviours.Description of dental care costs.

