### Statistical analysis plan

All the baseline and follow-up the individual- and tooth-level data, the parents’ and dentists’ TEI data, and costs’ information will be digitally registered (after training) for each codified patient in each centre keeping data safely stored and with limited access, in a designed data base in Microsoft Excel (2010), that includes data quality assurance by validation of data. The data will be sent to the DMT at each time point. Data will be analysed by an independent statistician. All statistical tests will be two-tailed tests. The level of statistical significance for all two-sided tests will be set at 0.05. Parametric methods will be considered first. Data that do not meet or cannot be transformed to meet parametric assumptions will be analysed by non-parametric methods. Demographic and clinical features of the participants (centre, gender, age, caries risk, pain, filling status, prs/PRS); oral health behaviour, dental care acceptability and costs, as well as caries experience (DMFS and dmfs with the D component using ICDAS-merged Epi) [35] will be described using mean and standard deviation (SD) for quantitative variables and percentages for qualitative variables.

Regarding costs, the providers’ payment model of the centre will be described (Fee-for-service, Capitation, Salary-based and Pay-for-performance) [43]. For the description of costs, these will be converted to the United States Dollar (USD) under the average Market Representative Exchange Rate for the year 2021 (MRER-average).

ANOVA and Kruskal Wallis analyses will be used to compare the baseline characteristics between centres.

The caries risk control (subjects where risk was reduced from high risk or maintained in low risk), and the number of subjects with avoidance of extraction, pain, and failure of restorations/sealants, will be compared between baseline (T0) and 12-month follow-up (T3) examinations using χ^2^.

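### Caries risk control counts staying low-risk and moving from high to low as one success, so the pooled figure and its T0–T3 change depend on the baseline risk mix

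*Protocol article*

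**What the plan says.** - **Entry** (Setting, participants and recruitment). Children qualify on age, general health and consent: "The inclusion criteria are children: (1) aged 3–5 and 6–8 years old; (2) generally healthy, and (3) have parental consent". The exclusions concern systemic disease or disability, plans to move, orthodontic appliances and attending another practice. None sets a caries or risk level.
- **Risk classes** (Baseline and follow-up oral examinations). A matrix of risk and protective factors is used for "classifying the patient’s caries risk into low or high". T0 and T3 have the full assessment for every child.
- **Outcome** (Secondary health outcomes). It is a single proportion over all children: "Proportion of subjects with avoidance of caries risk level increase/no control".
- **Definition and test** (Statistical analysis plan). Success is defined thus: "The caries risk control (subjects where risk was reduced from high risk or maintained in low risk". The result "will be compared between baseline (T0) and 12-month follow-up (T3) examinations using χ^2".
- **Care by risk class** (Interventions). "Low-risk patients receive the didactic aids but no behaviour change is conducted". High-risk children also have a shorter risk recall interval (3 months against 9).
- **Use of the risk strata elsewhere** (Statistical analysis plan). Low- and high-risk children are compared for parents' acceptability and for oral-health behaviour. No such split is stated for risk control.

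**The concern.** The definition joins two different events. One is an improvement in a child who started at high risk; the other is no deterioration in a child who started at low risk. The two groups start from different places and receive partly different care, and nothing in the article fixes or predicts their relative size. There is also no control arm with the same mix against which to read the result.

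A single proportion then cannot tell the reader how often high-risk children improved or how often low-risk children got worse. Two studies with the same results within each risk class could report very different headline figures. At stake is what this secondary outcome can say about the adapted system.

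**Working it through.** **The plan's own figure.** The article gives no expected value for risk control, so there is nothing to reproduce. Its sample size was derived for mean numbers of surfaces with progression and does not bear on this point.

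**Step 1: what the definition reduces to.** With two classes, a child reduced from high is low at T3, and a child maintained in low is low at T3. No other child is low at T3. Risk control is therefore the same as being low-risk at T3.

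**Step 2: formulas.** Let p be the share low-risk at T0, a the low-to-low rate and b the high-to-low rate.

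- Pooled control = p·a + (1 − p)·b
- Change in the low-risk share, T0 to T3 = p·a + (1 − p)·b − p = (1 − p)·b − p·(1 − a)

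Both contain p.

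**Step 3: numbers.** The article gives none of p, a or b, so all are assumptions. With a = 0.90 and b = 0.20:

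| Low-risk at T0 | Pooled control | T0–T3 change | High-to-low |
|---|---|---|---|
| 20% | 0.2×0.90 + 0.8×0.20 = 34% | +14 points | 20% |
| 50% | 0.5×0.90 + 0.5×0.20 = 55% | +5 points | 20% |
| 80% | 0.8×0.90 + 0.2×0.20 = 76% | −4 points | 20% |

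The change is zero where (1 − p)·0.20 = p·0.10, that is at p = 0.20/0.30 = 67%. Below that share the study shows a net gain and above it a net loss, with identical results inside each risk class.

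**Step 4: other assumed rates**, moving p from 20% to 80%:

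| a, b | Pooled control | T0–T3 change |
|---|---|---|
| 0.90, 0.30 | 42% to 78% | +22 to −2 points |
| 0.95, 0.20 | 35% to 80% | +15 to 0 points |
| 0.80, 0.40 | 48% to 72% | +28 to −8 points |
| 0.90, 0.00 | 18% to 72% | −2 to −8 points |

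In the last row no high-risk child improves, yet pooled control reaches 72% when 80% start low.

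**Step 5: the planned test.** Control is itself a change from T0 to T3, so it has no value at T0. The workable reading compares the low-risk share at the two visits, which is a paired comparison on the same children. An ordinary χ² treats the visits as independent. With a = 0.90, b = 0.30 and 206 children, it gives p-values of about 0.000001, 0.04 and 0.63 when 20%, 50% and 80% are low-risk at T0.

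**The case against.** The strongest reply is that the plan does not read the proportion alone but compares T0 with T3. On the first set of assumed rates, enrolling more low-risk children makes that contrast less favourable (+14, +5, −4 points). A reader might infer that pooling necessarily flatters the intervention. The planned comparison does not support that; the inflation appears only if the T3 proportion is read by itself, as the outcome list would allow. This part of the reply stands. It does not rescue the outcome, because the contrast still depends on the mix.

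Other points in the plan's favour:

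- Open entry is a legitimate design choice. Keeping low-risk children low is a proper aim of a risk-based system, and these children are not untreated. This stands; the difficulty is pooling without separation.
- Baseline caries risk will be described. This shows the mix but not the two success rates.
- The multilevel regression addresses surface-level data, not this child-level outcome.
- A separate analysis plan may tabulate the transitions. That is possible, but the article itself fixes the pooled definition and the comparison.

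A reader might also infer that a caries-free, low-risk child is almost certain to count as avoiding caries progression. The article gives no such rate, and its progression rule counts a sound surface that develops a lesion or receives a sealant or filling. Nor is a comparison of risk control between centres planned; only baseline characteristics are compared between centres.

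**Conclusion.** The concern holds for one component of the secondary outcomes. The primary outcome, at tooth-surface level, does not use this definition. The dependence on baseline mix follows from the definition and the two-class scale and needs no assumption. Its size does: with 90% low-to-low and 20% high-to-low, moving the low-risk share from 20% to 80% moves pooled control by 42 points (34% to 76%) and the T0–T3 change by 18 points (+14 to −4). The article states neither the expected mix nor the transition rates, so these figures illustrate the effect and do not forecast it.

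A reader might go further and treat the high-to-low proportion as the true effectiveness result. The design does not support that. Children picked out by an unfavourable classification and measured again without a control arm may improve through regression to the mean.

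**What to change.** In Secondary health outcomes and in the Statistical analysis plan:

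1. Report the full T0-by-T3 risk table.
2. Give two separate proportions with confidence intervals: high-to-low among children high-risk at T0, and low-to-high among children low-risk at T0.
3. Keep any pooled risk-control figure as a supplement only.
4. Replace the χ² for the overall T0–T3 change in risk class with a paired test, such as McNemar's.
5. Report child-level avoidance of caries progression by T0 risk class as well.
6. Do not describe the high-to-low proportion on its own as proof of effectiveness, and give regression to the mean as the reason.

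The cost is wording only, since risk class is already recorded for every child at T0 and T3. The price is wider intervals within each risk class and possibly a less favourable headline figure.

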
T0 and T3 include full 1D, 2D and 3D assessments. For intermediate T1 and T2 follow-ups, in 1D, all receive full oral-health behaviour reassessment, while risk is fully assessed only in patients previously classified as high-risk; in low-risk, only four risk/protective factors are reassessed (twice-a-day toothbrusing with ≥ 1000 ppm F, daily free-sugar intake above 50 g, dental biofilm and presence of new caries lesions). For 2D, all patients are clinically examined only for the latter. Subsequent 3D is derived. If in T1 or T2 the patient’s risk gets classified opposite to their previous assessment, both the recall interval and the reassessment are adjusted accordingly.

Parents’ and dentists’ acceptance of dental care will be assessed by an external researcher at T1, using designed TEI questionnaires (modified from Newton & Sturmey [40]).

Costs will be assessed in terms of duration and number of appointments regarding the type of care received (assessment/reassessment; individual level: risk/behavioral management, recall; tooth-surface level: NOC, TPOC;) and taking into account if the activity has been conducted solely by the examiner/CD, solely by a hygienist or both together, and country-level economic variables will be described [41–43].

Dropout criteria of a child from the study will include: (1) voluntary withdrawal from the trial by the patient/parents; (2) not attending the reassessments and in-office/remote appointments after three phone/message reminders.

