*AM* active monitoring, *NOC* non-operative care, *TPOC* tooth-preserving operative care, *ART* atraumatic restorative treatment, *NaF* sodium fluoride, *SDF* silver diamine fluoride

Interventions at both individual-and tooth surface level, will be conducted during the 12-month study period. After the 1-year follow-up (T3), no further interventions will be conducted for the study, but can be conducted separately if the centre decides to.

The strategies to improve adherence to interventions will include phone and text messages of next appointment reminders for parents and children; a remote communication channel with parents to answer questions and to motivate both the parents and the children to follow the study recommendations; reassuring the parents that in the practice the global SARS COV-2 biosafety guidelines including the use of PPE are being strictly followed. These strategies will also be used to promote participant retention and complete follow-up.

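### Avoidance of filling/sealant failure is read from status at T0 and T3, so a failure repaired like-for-like before T3 counts as avoided, and an unrepaired T0 failure counts as a failure

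*Protocol article*

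**What the plan says.** All references are to the Protocol article.

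- **Outcome.** Under Secondary health outcomes, one outcome is the proportion of children with control of caries risk and with "avoidance of extraction, pain, failure of the filling/sealant".
- **Analysis.** The Statistical analysis plan says that the number of children with "avoidance of extraction, pain, and failure of restorations/sealants, will be compared between baseline (T0) and 12-month follow-up (T3) examinations", by a chi-square test.
- **Measurement of fillings and sealants.** Baseline and follow-up oral examinations lists "presence and status of fillings (Optimal, Acceptable or Not acceptable) and sealants (Optimal or Not acceptable") among the surface-level scores. This is condition on the day of the examination.
- **Measurement of pain.** The same section records toothache with the sepsis index, "modified from the PUFA Index [39] with/without toothache". No recall period is stated.
- **Timing.** "T0 and T3 include full 1D, 2D and 3D assessments". For T1 and T2 the section says "For 2D, all patients are clinically examined only for the latter", which points back to a short list ending with biofilm and new lesions.
- **Care in between.** Under Interventions, "Interventions at both individual-and tooth surface level, will be conducted during the 12-month study period", and "clinical approaches/interventions include 5% NaF varnish at basic management, T1 and T2".

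**The concern.** Avoiding an event is a statement about an interval. Two examinations give status at two moments. The mismatch shows at T0: no follow-up has elapsed, so avoidance there can only mean that nothing is wrong on that day. Read the same way at T3, the outcome becomes the absence of a visible failure at month 12. It is no longer the absence of failure during the 12 months.

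For fillings and sealants this matters because glass-ionomer sealants, ART restorations and Hall crowns are the adapted care itself. How often they fail under non-aerosol conditions is a direct measure of its performance. If failures that were found and repaired drop out, the reported proportion also reflects how promptly each of the 21 centres repairs. With no control arm, nothing offsets that.

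The surface-level analysis does not recover these events. Its definition of progression covers a sealant that becomes a lesion, filling or missing tooth, and a filling that becomes a lesion or missing tooth. A sealant replaced by a sealant, or a filling by a filling, is neither.

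**Working it through.** The plan states no figure for this outcome, so there is none to reproduce. The check is first a reading of the sections together, then an illustration with assumed rates.

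**Reading.** Take a sealant placed at basic management.

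1. It fails in month 4. The T1 and T2 clinical examination does not name filling or sealant status, whichever of the listed items its restriction is taken to mean.
2. If nobody acts, it is scored Not acceptable at T3. The failure is counted correctly.
3. If it is replaced by a sealant, it is scored Optimal at T3. The failure is lost.
4. If it is replaced by a filling, the surface has visibly changed at T3 and also counts as progression. The event can be recovered.
5. Separately, a filling that was Not acceptable at T0 and was left alone is still Not acceptable at T3. It reads as a failure without a new event.

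Only case 3 overstates avoidance; case 5 understates it.

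**Formula.** All three inputs are assumptions:

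- r = share of children with a new filling/sealant failure in 12 months
- s = share of those children whose failures are all repaired like-for-like before T3
- c = share of children with no new failure who carry an unrepaired T0 failure to T3

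True avoidance = 1 − r. Avoidance seen at T3 = 1 − r(1 − s) − c. Net error = r × s − c.

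**Overstatement r × s, in percentage points, with c = 0:**

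| r | s = 0 | s = 10% | s = 25% | s = 50% |
|---|---|---|---|---|
| 5% | 0 | 0.5 | 1.25 | 2.5 |
| 10% | 0 | 1 | 2.5 | 5 |
| 20% | 0 | 2 | 5 | 10 |

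**Opposite error.** At r = 10% and s = 25%, 0.10 × 0.25 − c = 0 when c = 2.5%. A larger carry-over makes the reported figure too low.

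**Against sampling error.** I use N = 206, the size before dropout, and N = 567, the stated total if all centres finish with 27 children, with 95% Wilson intervals and c = 0. At N = 206 and r = 10%, 21 children fail and true avoidance is 185/206 = 89.8%.

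| Hidden by repair | Reported | 95% CI | Contains 89.8%? |
|---|---|---|---|
| 2 | 187/206 = 90.8% | 86.0–94.0 | yes |
| 5 | 190/206 = 92.2% | 87.8–95.2 | yes |
| 10 | 195/206 = 94.7% | 90.7–97.0 | no |

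Smallest number of hidden failures that puts the true value below the interval:

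| r | N = 206 | N = 567 |
|---|---|---|
| 5% | 7 of 10 | 11 of 28 |
| 10% | 9 of 21 (43%) | 15 of 57 (26%) |
| 20% | 12 of 41 | 19 of 113 |

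**Pain.** Toothache is lost only if it settles without extraction, is not registered as an emergency and is not recalled at T3. Assume 10% of children with toothache, a quarter ending in extraction, half of the rest settled before T3 without an emergency registration, and half of those not recalled: 0.10 × 0.75 × 0.5 × 0.5 = 1.9 points. With complete recall it is zero.

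**The case against.** **No rule for scoring failure is written down.** The plan gives a test and two time points, which could be the two ends of an interval, as in its definition of progression. The article condenses a fuller plan that Data Availability says can be requested, and event definitions often sit there. This stands in part. But the article does not leave the comparison open: it sets avoidance at T0 against avoidance at T3, and at T0 the word can only describe current status.

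**Interim data exist.** Care decisions are derived at T1 and T2, data are sent at each time point, emergencies are registered, and children who attend another practice are excluded, so repairs in retained children happen within the study. All of this stands. It narrows the problem and makes the fix cheap. It does not remove the problem, because the stated analysis uses only the T0 and T3 examinations.

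**Few failures may be found before T3.** The restricted T1 and T2 examination limits routine discovery, and a failure that is not found is not repaired. This stands, and it limits the size.

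**Status after a year of continuing care is a legitimate measure**, because retreatment belongs to the care system. That is fair as a description of the mouth at month 12. It is not what avoidance of failure says.

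A reader might go further and infer that the reported proportion must be too favourable, or that the whole composite is distorted. The documents support neither. Carried-over T0 failures push the other way, a tooth extracted for caries is still recorded as missing at T3, and the pain component depends on a recall period that is simply not stated.

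**Conclusion.** The point holds, as a minor one, for the filling/sealant component of one child-level secondary outcome. As written, the T0 versus T3 comparison counts a like-for-like repair before T3 as avoidance and an unrepaired T0 failure as a failure.

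Neither the size nor the direction of the net error can be derived. Under the assumed rates the overstatement runs from 0 to 10 points before any carry-over is subtracted. In the small case (2 of 21 failures hidden at N = 206) it lies well within sampling error. Nothing in the documents suggests repair rates as high as the 43% needed at N = 206 with a 10% failure rate.

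The primary surface-level outcome, the sample size and the main conclusion are not affected.

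**What to change.** Define the component as cumulative. Score a child as having a filling/sealant failure if any filling or sealant that was Optimal or Acceptable at T0, or was placed at basic management, is recorded as failed, repaired or replaced from the end of basic management to T3. Take this from the 3D care decisions at T1 and T2, the treatment records, and one added field at T1, T2 and T3 asking about filling/sealant repair or toothache since the last visit. The same field closes the gap for pain. Report the cumulative proportion with a 95% CI for each component, and keep T0 versus T3 status as description.

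The cost is a change of wording, one field at visits already planned, and linkage of records. The cost categories for non-operative and operative care do not separate a repair from new care, so they cannot replace that field.

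There are three drawbacks. The avoidance figure will probably be less favourable. Failures will still be undercounted where centres under-record. And a cumulative count has no baseline counterpart, so there is no T0 value to test it against.
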